| **Maintenance** | Screening for anxiety and depression | Proportion with sustained screening practices (% of AYHIV with a routine PHQ-2/9 at each visit) | Late (at month 12) implementation covering up to 12 months of adolescent treatment | Routine clinic patient records |
|  | Delivery of PRO-ACT intervention | Proportion with sustained treatment practices (% of AYHIV eligible for PRO-ACT with any PRO-ACT modules completed at each visit) |  | Checklist & patient records |
| **Acceptability** | Acceptability of PRO-ACT | Acceptability of PRO-ACT among AYHIV and providers in intervention clinics, assessed quantitatively and qualitatively | Early (month 3-6) and late (month 12) implementation and post-trial | Survey with HCW and post-trial FGDs and IDIs with HCW and AYHIV |
| **Appropriateness** | Appropriateness of PRO-ACT | Appropriateness of PRO-ACT among AYHIV and providers in intervention clinics, assessed quantitatively and qualitatively | Early (month 3-6) and late (month 12) implementation and post-trial | Survey with HCW and post-trial FGDs and IDIs with HCW and AYHIV |
| **SERVICE outcomes** | | | | |
| **Satisfaction with services** |  | Adolescent satisfaction with services received | Baseline and late implementation (at month 12) | Survey with enrolled adolescents |
| **Competency assessment** |  | ENACT assessment for providers | Pre-training, post-training, post-supervision | ENACT through EQUIP platform |
| **Self-efficacy** |  | Provider self-efficacy with implementing PRO-ACT | Baseline, month 3-6 and month 12 | Survey with HCW |
| **Provider satisfaction** |  | Provider satisfaction with services they offer, with the PRO-ACT training and supervision | Baseline, Post-training, and Post-supervision | Surveys with providers |

Aim 3: Economic evaluation

This aim will assess the following measures:

- Cost of PRO-ACT provider training and implementation
- Incremental cost-effectiveness: net added cost per case of depressive/anxiety/trauma symptoms resolved (health outcome)

*Additional exploratory outcomes*

- Cost per additional adolescent or youth with HIV with ≥80% adherence
- Cost per additional adolescent or youth with HIV virally suppressed

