| AIM 2: Assess implementation and service outcomes and determinants of implementation |  | FGDs with providers | Up to 30 with 7-10 participants each from the intervention and control facilities ≥18 years old |
|  |  | IDIs with providers | Up to 6 IDIs with providers from each participating clinic |
|  |  | FGDs with AYHIV | Up to 30 with 7-10 participants 16-24 years each from intervention facilities |
|  |  | Competence assessments using the ENACT tool | Up to 90 trained providers ≥18 years old at the 15 intervention clinics |
|  |  | Fidelity assessments using a standardized checklist | Up to 90 trained providers ≥18 years old at the 15 intervention clinics |
|  |  | Quantitative surveys with AYHIV | ~600 AYHIV involved in the intervention |
|  |  | Routine clinic records for AYHIV | All AYHIV in the 30 clinics ages 16-24 years |
|  |  | Checklist in the patient chart | All AYHIV (~2400) AYHIV 16-24 years in the study sites |
|  |  | Quantitative survey with facility/HIV clinic heads | 30 facility/ HIV clinic heads from selected study sites |
|  |  | Quantitative surveys with providers | Up to 6 providers from each of the 30 selected study sites |
| Aim 3: Conduct an economic evaluation of the intervention |  | Time in motion studies for provider time | Providers in the 30 adolescent HIV clinics |
|  |  | Interviews with program officers with information on program administration | 30 program officers in the HIV clinics |
|  |  | Quantitative surveys with AYHIV | ~600 AYHIV involved in the intervention |

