We will utilize the adapted WHO ENACT competency tool through the WHO EQUIP platform to assess trainee competencies at three time points: pre-training, post-training and post-supervision, to target training and supervision needs for the trainees. The ENACT competencies will be assessed through virtual role-plays using trained standardized patient actors based on standardized vignettes developed by the research team and validated by stakeholders and providers during the pilot study and rated on the EQUIP digital platform by trained raters. Each training group will have a maximum of 10 providers. Training follows the Apprenticeship model: it is interactive with opportunities to practice all modules with peer and trainer feedback.^123^ We will conduct didactic training through online platforms like Zoom, and reserve the in-person training within clinics for role-playing. We will also stagger the training to take place during the less busy days and hours, and train smaller pods of providers per clinic so that service delivery is not interrupted or compromised. After the training, the providers will implement the intervention among one or two AYHIV in their facilities whom they screen and have mild to moderate symptoms of psychological distress (depressive symptoms, anxiety symptoms or trauma symptoms), supervised by the training psychologists over 3-6 months. The supervision will ensure there is fidelity in screening and delivery of PRO-ACT.

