**7f. Assessing implementation of the intervention**

To assess the implementation of the intervention, the study will conduct the following procedures (summarized in Table 2).

Patient records will provide data on mental health screening using PHQ2/9 for AYHIV in 30 clinics, 6-months prior to the start of the study, and up to 24 months after site entry. These data will inform assessments of **reach** (~2400 records) and **maintenance** (~1200 records).

A checklist will be developed and will accompany patient charts (~2400 charts) and completed by clinic staff to assess implementation/fidelity of mental health screening. In the intervention sites (~1200 charts), the checklist will also be used to assess **implementation/fidelity** focusing on adherence to PRO-ACT by providers for ~300 AYHIV. Another checklist will be completed by the supervisors assessing **implementation/fidelity** during the review sessions with providers after completing PROACT sessions with study participants.

Study administrative records for the 15 sites will be used to track which study sites are trained and elect to deliver PRO-ACT, informing assessment of **adoption**.

A survey with providers in the intervention sites (~6 per site) will assess **readiness** to implement PRO-ACT, **acceptability**, **appropriateness** of PRO-ACT, **satisfaction** with services offered and the PRO-ACT training, and **determinants of implementation**. Those in the control sites will rate their **satisfaction** with services they offer AYHIV.

A survey with facility heads will assess structural **readiness** to implement PRO-ACT, barriers and facilitators to implementation and describe HIV and mental health **resources** and processes in the facility.

For trained providers in intervention sites (~6 per site), their **competence** pre-training, immediately after training and after completing supervision will be assessed using the WHO, EQUIP-developed ENACT provider competency assessment tool, within the virtual EQUIP platform. The providers will role play sessions with standardized patient actors trained using standard vignettes, which will be rated by study-trained raters within the study (following standardized/established EQUIP procedures as used in the Nairobi pilot of PRO-ACT).

Adolescent **satisfaction** with mental health services offered in clinics and cost of care, acceptability and appropriateness of PRO-ACT will be assessed using a survey.

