**9c. Other referrals:** During treatment sessions, it is also possible that providers will learn about issues such as child sexual and physical abuse in or outside the home or about parent/guardian depression or other serious mental health problems. Sexual abuse in Kenya is a notifiable offense. We will develop an emergency protocol that is within the framework of Kenyan legal requirements and organize for the survivors to be seen at the KNH Gender Based Recovery Centre, which is a “one stop” service in Nairobi County. Similar procedures will be outlined at the start of the study, in collaboration with clinic and county managers, for referrals in Homabay.

**9d. Quality of care and provider competence:** The study procedures do not interfere with routine care. The study will train providers to use a treatment approach with which they may be unfamiliar (psychological therapy). We will take precautions to ensure that the trained providers are able to safely deliver care to AYHIV. Providers who receive training in the PRO-ACT intervention will be clinical providers affiliated with public HIV clinics in 2 counties in Kenya. During the PRO-ACT training, trainers will closely observe trainees for their grasp of the material, ability to respond to changing situations during role-plays, and responsiveness to direction. In this study, we will use the ENACT competency assessment tool to assess provider competency; scores below the designated threshold will disqualify a provider from delivering the intervention. We will discuss each provider’s competency within the Kenya and UW research trainers and intervention experts.

Additional safety measures will include i) the training of the trainers on child protection and safety (i.e. all trainees will review and sign Child Protection or Vulnerable Adults policies, which provide them high-level guidelines for maintaining the safety of vulnerable groups); ii) articulation of a clear engagement and referral procedure when additional care is needed; and iii) as per University of Nairobi Research Ethics Committee requirements, depending on age, adolescents and their parent /guardian will sign an assent or consent form respectively.

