**12c. Overview of analysis plan**

***Analysis of the effectiveness of PRO-ACT***

***Primary analyses:*** Primary analysis of the effectiveness of PRO-ACT will be conducted at 6- and 12-month follow-up. Mental health data for the primary analyses including assessments for depressive, anxiety and trauma symptoms will be collected at baseline, and follow up at months 3, 6, 9, and 12 for AYHIV with mild to moderate symptoms in intervention and control clinics. Assuming that most or all participants have completed the intervention by then, the 6-month analysis provides an estimate of the near-term treatment effect, while the 12-month analysis examines treatment effect sustainability. Both 6- and 12-month analyses will employ random coefficients models to account for clustered data structure, and compare outcome means separately (depression, anxiety, trauma) between the treatment and control groups. These models will include baseline symptom scores as predictors, as well as county, demographics, school (boarding vs. day), and clinic type (youth specific vs. integrated)as covariates. The impact of these covariates as treatment moderators will be examined. Model assumptions will be checked, including normality, linearity of effects, additional predictor interactions, and power-terms, including among baseline mental health scores (e.g., anxiety x depression interaction). We will then add provider competency to the final outcome models to examine its role as a mediator of the treatment effect.

***Secondary analyses:*** Viral load data will be abstracted from clinic records at baseline, month 6 and month 12. Viral suppression analyses at 6- and 12-month follow-ups will use similar clustered data models for the group randomized structure and strategies, as described for the analysis of the mental health outcomes, however for a binary response (i.e., relative risk regression). The same covariates and interactions will be included in the model with the treatment/control indicator variable. Model assumptions of effects and additional interactions will also be checked.

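### Provider competency is planned as a mediator in the two-arm outcome models but is measured only in intervention clinics, so the mediated and direct effects are not identified without unstated assumptions

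*Protocol*

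**What the plan says.** **The analysis.** Protocol section 12c, under the primary analyses, uses random coefficients models at 6 and 12 months that "compare outcome means separately (depression, anxiety, trauma) between the treatment and control groups", adjusted for baseline scores and other covariates. It then adds: "We will then add provider competency to the final outcome models to examine its role as a mediator of the treatment effect".

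**The measurement.** Wherever the protocol says who has competency rated, it names PRO-ACT trainees:

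- Table 3 (section 5d), ENACT row: "Up to 90 trained providers ≥18 years old at the 15 intervention clinics".
- Section 7c: ENACT is used "to assess trainee competencies at three time points: pre-training, post-training and post-supervision".
- Section 7f gives the timing for about 6 trained staff in each intervention clinic: "pre-training, immediately after training and after completing supervision will be assessed using the WHO, EQUIP-developed ENACT provider competency assessment tool".
- Table 2 (section 3b) names no arm, but its time points are training time points: "Pre-training, post-training, post-supervision".

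Section 9d adds that "scores below the designated threshold will disqualify a provider from delivering the intervention".

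**Control clinics.** Section 5f gives them standard of care. Their providers take part in interviews and complete a survey on sociodemographics, satisfaction and self-efficacy (sections 7f and 11a). No competency rating is scheduled for them.

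**The concern.** A mediation analysis splits the randomised effect into a part that runs through the mediator and a part that does not. It needs the effect of arm on the mediator, and the relation of mediator to outcome with arm held fixed. If the mediator is recorded in one arm only, the data carry no information on the first of these, and the direct effect cannot be separated from the intercept.

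What is at stake is a supporting claim about mechanism. The trial could report that competency explains some share of the PRO-ACT effect when that share was set by how the empty control values were handled. Self-efficacy is surveyed in both arms, but it is a different construct and cannot stand in for a rated competency.

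**Working it through.** **1. Who is rated.** Inputs: 15 intervention clinics and up to 6 trained providers per clinic (Table 3, section 7f). 15 × 6 = 90, which reproduces the protocol's own figure and leaves 0 from the 15 control clinics.

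**2. How many participants lack a value.** Section 12a expects 10 to 20 participants per site, so 15 × 10 = 150 to 15 × 20 = 300 controls; Table 3 gives about 300 per arm. Competency is missing for 100% of them, half of the trial population.

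**3. Complete cases.** Let T be arm, M competency and Y a symptom score. Leaving out covariates and clinic effects, the two models are

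- outcome: Y = b0 + b1·T + b2·M
- mediator: M = a0 + a1·T

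With 30 clinics × 20 participants = 600 and M recorded only where T = 1, 300 complete cases remain, none of them controls. T then equals 1 throughout and duplicates the intercept. The outcome design matrix has rank 2 of 3 and the mediator design matrix rank 1 of 2. Neither the direct effect b1 nor the path a1 can be estimated. Only b2, the slope within the intervention arm, survives.

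**4. A constant c entered for controls.** M now has no spread among controls, so b2 still comes from the intervention arm alone. With D the difference in mean outcome between arms and M̄1 the mean competency in the intervention arm:

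- b1 = D − b2·(M̄1 − c)
- apparent mediated share = 1 − b1/D = b2·(M̄1 − c)/D

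The share is linear in c, and no trial data inform c. As an illustration, one data set was simulated with 30 clinics of 20, a true direct effect of zero, an arbitrary score scale and ordinary least squares. It gave D = −0.578 and b2 = −0.336, so the share moves by 0.336/0.578 = 0.58 for each unit of c:

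| c | b1 | apparent mediated share |
|---|---|---|
| 0 | 0.461 | 180% |
| 1 | 0.125 | 122% |
| 2 | −0.210 | 64% |
| 3 | −0.546 | 6% |
| 4 | −0.882 | −52% |

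(Shares are from unrounded coefficients.) With M known in both arms, the same data gave b1 = −0.174 and a share of 1 − 0.174/0.578 = 70%. These percentages show how the answer depends on c. They are not sizes to expect in this trial.

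**5. Pre-training scores as c.** The trainees' pre-training ENACT ratings are an observed level of untrained competency in randomised clinics, so c would no longer be arbitrary. For this to identify the mediated effect, three things must hold:

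- untrained competency does not drift between the pre-training rating and the trial period;
- trainees, whom the clinic head selects purposively (section 5e), are comparable with the control providers;
- competency acts on outcome in the same way in both arms.

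The protocol states none of these and does not propose the proxy.

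**The case against.** The strongest reply is that the gap is narrower than it looks. Four parts of it stand.

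- **Mediation impossible under any assumptions.** A reader might infer this. The documents do not support it, because pre-training scores are planned and could serve as a proxy. What holds is that the effects are not identified without assumptions the protocol leaves unstated.
- **The treatment effect itself distorted.** A reader might infer this too. Section 12c adds competency to models already fitted for the treatment comparison, so the 6- and 12-month effectiveness estimates do not depend on it.
- **Any control value makes competency nearly a copy of arm.** This is not so. With equal arms, and d the distance from c to M̄1 in within-arm standard deviations, the correlation of arm with competency is 0.5d/√(0.5 + 0.25d²): 0 at d = 0, 0.33 at d = 0.5, 0.58 at d = 1 and 0.82 at d = 2. The fault is that c is arbitrary, not that collinearity is inevitable. Centring competency at the intervention mean with 0 for controls is the case d = 0: the model has full rank and the treatment coefficient is not displaced, but it describes variation by competency and not mediation.
- **The disqualification threshold.** Section 9d gives neither its value nor the number of providers expected to fall below it. It may narrow the range of competency among delivering providers, by an amount that cannot be stated.

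The objection that this can be left to a statistical analysis plan does not stand. Such a plan can choose a mediation estimator, but the protocol fixes both the analysis and who is rated, and the two do not fit.

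**Conclusion.** The point holds for the mediation analysis only. As written, competency is missing for the whole control arm (150 to 300 participants, about 300 by Table 3), and neither the effect of arm on competency nor the direct effect is identified. What can be learned from the planned data is the association of competency with outcome among at most 90 providers in 15 clinics.

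This rests on reading Table 2, which names no arm, in line with Table 3 and sections 7c and 7f; its training time points leave little room for another reading. It is a flaw in a supporting analysis and leaves the primary comparison intact. It should be settled while ratings can still be added, because missing control ratings cannot be recovered afterwards.

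**What to change.** Replace the mediation sentence in section 12c with an exploratory analysis confined to the intervention arm: participant outcome regressed on the delivering provider's post-supervision ENACT score, adjusted for baseline symptom score, with clustering accounted for. Report it as an association and not as mediation, and note that the threshold in section 9d may narrow the range of scores.

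**Cost.** The mediation claim is given up. Each participant must be linked to a provider; the modules checklist in section 11a, which providers keep for each participant and visit, could carry that link. The analysis will be thin, at about 300/90 ≈ 3 participants per provider. Limiting it to participants who took up PRO-ACT selects on something that happens after randomisation, which is a further reason to claim no more than association.

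**If mediation is to be kept**, there are two routes. One is to rate ENACT in control-clinic providers at times matching the intervention clinics. This is an added procedure, although up to 6 providers at each of the 30 sites are already to be surveyed and the role-plays are virtual. The other is to name the pre-training scores as the control reference and write out the assumptions in step 5 of the working.

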**5f. Randomization procedures**

For the cluster randomized controlled trial, the 30 clinics will be randomized to intervention and control clinics. Clinics will be randomized using computer generated random numbers to either intervention or control status, using restricted randomization to balance for county. Randomization will be performed at UW by a biostatistician with access only to the clinic characteristics of interest. After randomization, the list of clinics and allocation arms will be given to the study team. Fifteen clinics will receive standard of care (screening and referral to available services) and 15 will receive the intervention (screening, PRO-ACT and referral to available services where applicable).

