**12.** **STATISTICAL CONSIDERATIONS**

**12a. Sample Size Considerations**

**Aim 1:** *Stakeholders’ workshop:* We estimate that 40 purposively selected participants for the stakeholders’ workshop will be sufficient to provide diverse information leading to the contextual adaptation of the intervention and the implementation process. Our previous work to develop interventions in Kenya has included 30-40 stakeholders which has been sufficient to reach saturation in perspectives.

**Aim 2**: *Cluster randomized controlled trial:* From previous work, we anticipate about 25% of adolescents and young adults in each clinic will have mild to severe mental health scores and enroll in the study. We anticipate enrolling 10 to 20 participants from each of 30 sites. Table 1 contains conservative estimates of statistical power to detect a range of smaller (Cohen’s *d* = 0.2, 0.3, and 0.4) effects under different study scenarios for an alpha value of 0.05. They are conservative estimates because they assume little predictive power of covariates in the random coefficients models (i.e., R^2^ values of 0.05 for the individual level and 0.01 at the site level).

| **Table 5: Conservative power estimates** | | | | | | | | | |
| --- | --- | --- | --- | --- | --- | --- | --- | --- | --- |
|  | Intraclass correlation values | | | | | | | | |
| Number of participants per site | 0.01 | | | 0.03 | | | 0.05 | | |
| ‍ | Effect size | | | Effect size | | | Effect size | | |
|  | **0.2** | **0.3** | **0.4** | **0.2** | **0.3** | **0.4** | **0.2** | **0.3** | **0.4** |
| 10 | 0.37 | 0.69 | *0.91* | 0.33 | 0.62 | *0.86* | 0.29 | 0.56 | *0.81* |
| 20 | 0.6 | *0.91* | *0.99* | 0.48 | *0.82* | *0.97* | 0.40 | 0.73 | 0.93 |

**Aim 2:** *Implementation outcomes:* Table 6 contains the minimum detectable effects for binary and continuous implementation science outcomes under the design described above. These power estimates are for a power of 0.8, alpha of 0.05, and R^2^ = 0.05.

| **Table 6: Minimum detectable effects for implementation science outcomes** | | | | | | | |
| --- | --- | --- | --- | --- | --- | --- | --- |
| **Binary outcomes** | | | | | | | |
| ‍ | Minimum proportion difference from 0.8 | | |  | Minimum proportion difference from 0.4 | | |
| ‍ | Intraclass correlation values | | |  | Intraclass correlation values | | |
|  | 0.01 | 0.03 | 0.05 |  | 0.01 | 0.03 | 0.05 |
| Reach (~80 per site) | 0.73 | 0.71 | 0.69 |  | 0.32 | 0.30 | 0.28 |

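### The viral-suppression model in 12c does not name baseline suppression as a covariate, and it puts interactions beside the treatment term without saying how the overall relative risk is obtained

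*Protocol*

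**What the plan says.** Section 12c describes the symptom models first. They compare outcome means between arms, and their covariates are listed: "These models will include baseline symptom scores as predictors, as well as county, demographics, school (boarding vs. day), and clinic type". Each symptom outcome therefore has its own baseline value in its model. Moderation of the treatment effect by these covariates is something to be examined, and predictor-by-predictor interactions (the example is anxiety by depression) are part of checking the model.

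The secondary-analysis paragraph then turns to viral suppression. It states that "Viral load data will be abstracted from clinic records at baseline, month 6 and month 12". It adopts similar clustered models and strategies, now as relative risk regression for a binary response, and adds: "The same covariates and interactions will be included in the model with the treatment/control indicator variable".

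The paragraph does not name baseline suppression as a covariate. It does not mention a main-effects model, centring or standardisation for the overall relative risk. Section 12a gives power for symptom effect sizes and detectable effects for implementation outcomes, but nothing for viral suppression.

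**The concern.** Two things in the quoted sentence are fixed badly.

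1. **The covariate list fits another outcome.** In the symptom paragraph the point of "These models will include baseline symptom scores as predictors" is to adjust each outcome for its own starting level. Carried over unchanged, the list adjusts suppression for symptom scores and not for baseline suppression, which is plausibly the better predictor and is already in the data. Randomisation is restricted to balance county (section 5f). With 15 clinics per arm, nothing named in the design or the model deals with a chance difference between arms in baseline suppression.

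2. **The wording on interactions is stronger here than elsewhere.** For symptoms and for implementation outcomes, 12c has interactions examined or checked. For suppression it has them included alongside the treatment indicator. If they are treatment-by-covariate terms, the treatment coefficient under ordinary dummy coding is the log relative risk in one reference subgroup. The plan does not say which quantity is reported as the trial's result.

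At stake are the precision and the meaning of the one secondary effectiveness estimate, for which no power is stated.

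**Working it through.** **Inputs from the protocol.** 30 clinics, 15 per arm ("Fifteen clinics will receive standard of care (screening and referral to available services) and 15 will receive the intervention"). Cluster size: "We anticipate enrolling 10 to 20 participants from each of 30 sites". Alpha 0.05 ("effects under different study scenarios for an alpha value of 0.05"; sidedness is not stated, so two-sided is assumed). Covariate strength in the power table: "R^2^ values of 0.05 for the individual level and 0.01 at the site level".

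**Inputs assumed, because the protocol gives none for suppression.** Suppression rate 0.80; correlation ρ between baseline and follow-up suppression 0.2 to 0.7; ICC 0.01 to 0.05 (the range of the symptom power table).

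**Step 1: reproduce the plan's own figure.** For a standardised outcome with n per clinic,

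Var = 4[ICC(1 − 0.01) + (1 − ICC)(1 − 0.05)/n]/30, with a noncentral t on 28 df.

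For n = 20, ICC = 0.03, d = 0.3: 4[0.0297 + 0.046075]/30 = 0.010103, SE = 0.1005, noncentrality 0.3/0.1005 = 2.98, power 0.821. The protocol's power table in 12a shows 0.82. All 18 cells agree to within 0.005. The variance structure is therefore the plan's own.

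**Step 2: add baseline suppression.** On the risk-difference scale, as an approximation,

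Var = 4p(1 − p)[ICC + (1 − ICC)(1 − ρ²)/20]/30.

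The adjustment is credited only with reducing within-clinic variance. Worked example at ICC 0.03, ρ = 0.5: the bracket goes from 0.03 + 0.97/20 = 0.0785 to 0.03 + 0.97 × 0.75/20 = 0.066375. The variance ratio is 0.846 and the SE ratio 0.92. At ρ = 0.6 the variance ratio is 0.778.

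| ICC | ρ | SE without | SE with | Ratio | Detectable difference, 80% power (27 df) |
|---|---|---|---|---|---|
| 0.01 | 0.2 | 0.0356 | 0.0350 | 0.98 | 0.104 → 0.102 |
| 0.01 | 0.5 | 0.0356 | 0.0317 | 0.89 | 0.104 → 0.092 |
| 0.01 | 0.7 | 0.0356 | 0.0274 | 0.77 | 0.104 → 0.080 |
| 0.03 | 0.5 | 0.0409 | 0.0376 | 0.92 | 0.119 → 0.109 |
| 0.05 | 0.2 | 0.0456 | 0.0452 | 0.99 | 0.133 → 0.131 |
| 0.05 | 0.5 | 0.0456 | 0.0427 | 0.94 | 0.133 → 0.124 |
| 0.05 | 0.7 | 0.0456 | 0.0398 | 0.87 | 0.133 → 0.116 |

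The saving in SE runs from about 1% to about 23%.

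One illustration in terms of power, with assumed rates of 75% and 85%, 20 per clinic and ICC 0.03: the mean of p(1 − p) is (0.1875 + 0.1275)/2 = 0.1575, so Var = 4 × 0.1575 × 0.0785/30 = 0.00165 and SE = 0.0406. Power on 28 df is 0.66. It becomes 0.73 at ρ = 0.5 and 0.77 at ρ = 0.6.

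**Step 3: the interactions.** A clustered log-Poisson model was simulated with 30 clinics of 20, 10 clinics per county and an effect that differs by county and school (all assumed; 300 runs per setting). Without treatment interactions, the arm coefficient averaged a log relative risk of 0.070 to 0.082 (empirical SE 0.040 to 0.049). With uncentred treatment-by-covariate interactions, the coefficient on the arm term averaged 0.020 to 0.051 (SE 0.103 to 0.115, that is 2.3 to 2.6 times as large). The second coefficient estimates a different quantity: the effect in the reference subgroup.

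A separate simulation on a continuous scale (same size, ICC 0.03) shows that coding drives this. Mean SE(arm) was 0.105 with main effects, 0.231 with five uncentred interactions, and 0.105 with the same five interactions mean-centred. For the average effect, the interactions cost essentially nothing.

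**The case against.** The strongest reply is that 12c is an overview, and that coding, centring and the reported contrast are usual content of an analysis plan that is not shown. The paragraph also adopts the symptom-model strategies, which can be read as an arm comparison followed by a look at moderators. By analogy, the symptom strategy adjusts for the outcome's own baseline, so baseline suppression may be intended, and nothing excludes it. The only interaction given as an example is predictor-by-predictor, and such a term leaves the meaning of the treatment coefficient unchanged. Finally, omitting a baseline covariate causes no bias under randomisation.

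Much of this stands, and it limits the point. A reader might infer that the plan misses the overall effect altogether, or that its standard error doubles and its power collapses. The protocol does not support that. It nowhere says that an uncentred reference-subgroup coefficient is the reported result, and the inflation vanishes when the terms are centred. A reader might also extend the complaint to the three symptom models. There the moderators are only to be examined, and nothing says that they stay in the model that gives the treatment effect.

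What the reply does not remove is the sentence itself. It goes beyond silence: it specifies the same covariates, from a list that names another outcome's baseline, and it says that interactions are included.

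**Conclusion.** The point holds in limited form. As worded, the suppression model names no baseline suppression and places interactions beside the treatment term without stating an overall relative risk.

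The cost of the first gap is precision: about 1% of the SE at correlation 0.2 and ICC 0.05, and about 23% at correlation 0.7 and ICC 0.01, with 20 per clinic. It is negligible at the low end and material at correlations of 0.5 or more with a low ICC. The size rests on a suppression rate, correlation and ICC that the documents do not give. Chance imbalance in baseline suppression also stays unadjusted; this is a matter of precision and credibility, not of bias.

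The second gap is one of definition. It matters only if the interactions are treatment-by-covariate terms and the uncentred coefficient is reported.

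**What to change.** In the secondary-analysis paragraph of 12c:

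- Take the overall relative risk at 6 and 12 months from a model with arm, county, the listed covariates and baseline viral suppression, with a category for missing baseline and no treatment interactions. Alternatively, prespecify a standardised (marginal) relative risk.
- Examine moderators in separate models labelled exploratory.
- Code baseline suppression at the same cut-off as the outcome. Section 3b has to be reconciled first: its text defines suppression as below 200 copies/ml, while Table 1 labels below 1000 as suppressed and below 50 as undetectable.

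The cost is wording only. Baseline viral load is already abstracted, so no new data collection is needed.
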